### Variables and statistical analysis plan

#### Qualitative variables

All variables will be first explored by missing analysis at three levels: at center level; at country level; at geographic area level.

Histology obtained at the back-table graft preparation, or alternatively at any time before graft implantation, will constitute a key point although not a mandatory condition for the enrollment. The histology slides will be scanned at the local centers, de-identified and uploaded on the eCRF, and centrally read for research purposes.

Transplant candidates CT scan (DICOM files only) from the pre-listing work-up will be de-identified and uploaded on the eCRF and centrally read for research purposes.

The incidence and grade of ischemic cholangiopathy will be measured by means of a cholangio-MR at 10–12 months after LT (on-demand, based on clinical suspicion of ischemic cholangiopathy for all grafts, e.g., higher than twofold increase in baseline alkaline phosphatase levels). The DICOM files will be anonymised and uploaded on the eCRF and centrally read for research purposes.

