## Introduction

During the last decade, the expansion of the donor pool using extended criteria (ECD) and donation after cardiocirculatory death donors (DCD) has resulted in heightened attention to allograft failure (AF) due to ischemia–reperfusion injury after liver transplantation (LT). The prompt diagnosis of AF is paramount to defining the indication for early retransplantation. Moreover, the grafts from ECD and DCD may develop early AF during the initial 90 days [1, 2] and delayed AF, primarily due to ischemic cholangiopathy [3]. LT from living donors (LDLT) is a growing procedure worldwide. However, the prevalence of steatosis in the general population is growing, too. A safety threshold for graft steatosis has yet to be entirely investigated, and the possible role of mitigation strategies to reduce the risk of AF in LDLT is a critical unmet need.

The evaluation times and the modalities to promptly identify AF are still the object of research. No consensus exists on the most accurate predictors and indicators of AF, neither on potential mitigation strategies [4–11]. In addition, ECD and DCD grafts are burdened by a higher incidence of ischemic cholangiopathy [12], which typically develops after 6–12 months, which is also a cause of AF and need for retransplantation. With the intent to further expand and optimize the donor pool, machine perfusion (MP) technologies are increasingly employed, allowing utilization of organs that have traditionally been discarded. Moreover, MP allows extended preservation times and assessment of graft viability, especially when considering organs with multiple risk factors (e.g., elderly donors, steatotic grafts, post-anoxic grafts, etc.). [13]

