Secondary (#5)	To identify the best-time for re-transplant (after stratification according to the post-operative weeks, months, trimesters);
Secondary (#6)	To investigate differences in the incidence of allograft failure and ischemic cholangiopathy at 90 and 365 days according to standard DBD, DCD and high- risk DBD, LD donor grafts;
Secondary (#7)	To evaluate the effect of mitigation strategies on the precipitating factors of Allograft Failure at 90 and 365 days;
Secondary (#8)	To investigate the association of kinetic algorithms with development of post- LT complications (acute kidney injury, ischemic cholangiopathy, other complications);
Secondary (#9)	To identify risk factors for mortality that may contraindicate re-transplant;
Secondary (#10)	To investigate the impact of donor-to-recipient gender match on LT outcomes

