## Methods

### Study design, steering committee, and participating centers

This is a multicenter, international, non-competitive, observational two-segment study.

The study segments include a first one with retrospective patient enrollment and a second one with prospective enrollment (Table 3).

**Table 3 Tab3:** Study design and population

	Prospective segment (high-volume centers ≥ 65 transplants per year)	Retrospective segment (low- & intermediate- volume centers < 65 transplants per year)
Sample size	750	4200
Consecutive pts to be included	50	75
No. of Centers to be involved	15	56
Enrollment period	July ‘21–December ‘23	January ‘17–December ‘19
Data entry period	Up to January’25 (follow-up)	Up to October’24 (follow-up)
AIMs	Development/validation of NEW/previous prognostic algorithms	Validation of previous kinetic algorithms
Main parameters	AST, PLT, BIL, INR	AST, PLT, BIL, INR
Outcome data and follow-up	Incidence of AF at 90 and 365 days Comprehensive complication index Length of stay in ICU, length of stay in hospital 90d and 365d graft survival, 90d and 365d patient survival, 90d and 365d ischemic cholangiopathy-free survival Actuarial data at 12 months	Incidence of AF at 90 and 365 days Comprehensive complication index Length of stay in ICU, length of stay in hospital 90d and 365d graft survival,90d and 365d patient survival, 90d and 365d ischemic cholangiopathy-free survival Actuarial data at 48 months
Pre-operative assessment	Yes	No
Sarcopenia		Yes
Malnutrition		Yes
Cardiac risk		Yes
Renal risk		Yes
Biopsy of the graft (back table)	DBD, DCD	Only when available
Post-operative assessment of factors that favour or contraindicate re-transplant	Yes	No
Number of parameters to be recorded	297	241
Number of calculated fields	27	24

Prospective and retrospective segments

A steering committee (SC) was constituted to design the study (Fig. 1). Members were identified according to their experience on the topic and their geographic area (Europe, Americas, and Asia).

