### Outcome measures

Allograft failure (AF) was defined as graft failure (leading to retransplant or death) for any reason at day 90 and at day 365 after LT. This definition also captures all late-occurring AFs (also known as delayed non-function) [34, 35] We consider as AF determinants all those events potentially affecting the process of graft function recovery, independently if they were strictly associated with ischemia–reperfusion injury. Indeed, vascular (thrombosis of the hepatic artery or portal vein), biliary, toxic, and major hemodynamic events will be included, because any of them can interact with parenchymal dysfunction, affecting graft function recovery and favoring graft failure and death.

Other outcome measures are comprehensive complication index, intensive care unit length of stay, hospital length of stay (LoS), and cholangiopathy-free survival at 90 and 365 days, graft and patient survival at 90 and 365 days,

The prospective cohort dataset includes 297 data entries and 27 calculated parameters (see supplementary material 1). Variable domains are:identification datadonor characteristics datarecipient preoperative datagraft histology dataintraoperative datarecipient postoperative datastudy endpoints dataoutcome and follow-up data.

The electronic Case Report Form (eCRF) was developed using the REDCap ver 10.0.21 software hosted at https://redcap-irccs.policlinicogemelli.it/. The eCRF allows easy calculation of scores including L-GrAFT and EASE scores.

The REDCAP software performs de-identification and encryption of the data.

The retrospective segment dataset includes 241 variables (supplementary material) to be collected from each center’s previously existing databases.

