## Discussion

This protocol refers to the first global study on liver transplantation outcomes. The study design includes several objectives based on LT practice worldwide, with centers participating in a balanced manner depending on their country’s location and activity. In addition to cross-sectional information, we expect to acquire a large volume of data to develop new models for predicting AF at different time points.

First, it will be paramount to build a new model for predicting early AF (i.e., 90-day post-LT allograft failure) based on a multicenter international comprehensive retrospective and prospective data collection. The work set by the steering committee stands on the background of the existing kinetics-based scores (L-GrAFT and EASE) constructed from a single center and a multicenter two-nation setting, respectively. Compared to these two scores, the models we aim to develop imply the advantage of a wider setting (60 centers, 21 countries, from 6 world areas) and a prospective patient enrollment. In addition to standard transplant outcome measures (graft failure and patient death at 90 and 365 days), we will pay attention to hospital and ITU length of stay, the incidence of weaning/extubation failure [57], as well as surgical complications. [58–60] Furthermore, we expect the study to allow us to develop and validate model(s) with increasing predictive accuracy from the 3rd to 7th postoperative day, making them more usable for all-day practice, bringing forward the availability of prognostic tools in the first few days after LT. We expect these tools to be able to weigh the risk of death without retransplantation and aid the decision-making processes for transplant physicians.

The presence of a retrospective study segment composed of high- and medium-volume centers guarantees a second-layer control of the applicability of previous models as well as the potential backward test of new models to real-world scenarios. The existing kinetic-based scores will be tested on the retrospective data with the aim of validating them on a large scale on a broad variety of liver transplant centers across different countries.

Second, we extended the evaluation time to 365 days, with the intent of capturing those failures occurring at a later stage. Late failure is increasingly seen nowadays due to the growing utilization of DCD and ECD grafts and the subsequent loss of grafts from ischemic cholangiopathy.

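### Ischemic cholangiopathy incidence is assigned to an on-demand MR at 10–12 months, a method that cannot supply the planned 90-day analysis or count grafts lost to it before month 10

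*Protocol article*

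**What the plan says.** **Measurement.** The Qualitative variables section of the protocol article reads: "The incidence and grade of ischemic cholangiopathy will be measured by means of a cholangio-MR at 10–12 months after LT". The parenthesis that follows limits who is scanned: "on-demand, based on clinical suspicion of ischemic cholangiopathy for all grafts", with a rise in alkaline phosphatase as the example trigger. The images are then read centrally.

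**Analysis.** Secondary objective #6 in Table 2 is worded "To investigate differences in the incidence of allograft failure and ischemic cholangiopathy at 90 and 365 days", by donor category. Table 3 lists "90d and 365d ischemic cholangiopathy-free survival" in the columns for both the prospective and the retrospective segment. Outcome measures repeats "cholangiopathy-free survival at 90 and 365 days".

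**Natural history.** The Introduction describes ischemic cholangiopathy as a condition "which typically develops after 6–12 months, which is also a cause of AF and need for retransplantation". The Discussion explains the extension of follow-up to 365 days partly by the "subsequent loss of grafts from ischemic cholangiopathy".

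**The concern.** The outcome is analysed at two time points, but the only stated way of measuring its incidence is one scan near the second of them, in patients selected by suspicion. A scan at 10–12 months can show that disease is present. It cannot show that disease was present some seven or more months earlier, at day 90. Nor can it be done on a graft already lost to death or retransplant, and the article itself says that cholangiopathy causes such losses.

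At stake is the donor-type comparison in objective #6 and, less directly, objective #8, which relates kinetic scores to complications including cholangiopathy. If the chance of being classified varies with graft type, a difference in recorded incidence mixes a difference in disease with a difference in detection.

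**Working it through.** The document gives no rate, sample size or power for cholangiopathy, so there is no figure to reproduce. The check compares the stated method with each stated use.

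**1. Day 90.** The scan window opens at month 10 and day 90 is about month 3, so the gap is 10 − 3 = 7 months at least, and up to 12 − 3 = 9 months. The Introduction says the condition "typically develops after 6–12 months", so few events by day 90 would be expected anyway. The article gives no earlier assessment and no rule for back-dating. Under the stated method, 90-day incidence cannot be determined, and 90-day cholangiopathy-free survival has no cholangiopathy component.

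**2. Day 365.** By one year, a patient who develops cholangiopathy is in one of three positions:
- graft in place at month 10, disease suspected, scan done: classified;
- graft in place at month 10, disease not suspected: not scanned, so not recorded;
- graft lost or patient dead before month 10: cannot be scanned in the window.

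For graft type g, let π be the true one-year risk, ℓ the fraction of cases lost before the window, and v the fraction of the remaining cases that are suspected and confirmed. Then

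recorded incidence(g) = π(g) × [1 − ℓ(g)] × v(g),

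and the recorded ratio of type 1 to type 2 is

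[π(1)/π(2)] × [(1 − ℓ(1))/(1 − ℓ(2))] × [v(1)/v(2)].

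The ratio is undistorted only if (1 − ℓ) × v is the same in both types. A larger ℓ in high-risk grafts pulls their recorded incidence down. A larger v, because clinicians look harder in those grafts, pushes it up. The document gives neither quantity for any graft type, so neither the size nor the net sign can be calculated.

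**3. Retrospective segment.** Its transplants date from January 2017 to December 2019. For the last of them, month 12 falls in December 2020, before prospective enrollment began in July 2021. A study-timed scan therefore cannot be imposed on this segment, and Outcome measures says its variables come from databases the centers already held. By Table 3 the segment is 4200 of 750 + 4200 = 4950 patients, or 4200/4950 = 85%. The same two cholangiopathy outcomes are listed for it.

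**4. Other biliary data.** The Quantitative variables section says anastomotic and non-anastomotic biliary complications will be evaluated by graft type. It gives no assessment time and does not define cholangiopathy from them.

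**The case against.** The strongest reply is that the imaging sentence describes only the centrally read component. Biliary events are among the failure determinants, non-anastomotic complications are evaluated by graft type, and hospital notes and pathology results are named data sources. The variable list and the definitions are in supplements not shown here. Since a timed scan cannot serve the retrospective segment, most of the cohort must be ascertained in some other way. This stands to the extent that a reader might infer that early cases are never classified, and the documents do not support that: dated diagnoses may well be recorded. It does not remove the conflict, because the article expressly assigns incidence, and not only grade, to the scan. The retrospective segment makes a records-based definition more necessary.

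A second reply is that cholangiopathy-free survival may count death and graft loss as events, so early losses would enter that endpoint. This is possible, though the article does not say so. It would not rescue the separate incidence in objective #6.

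Two stronger readings are tempting and should not be drawn:
- **A count of missed cases.** The sizing section uses 6% allograft failure overall, which gives 0.06 × 750 = 45 prospective patients, and hypothesises 10%, 7% and 4% by donor category. These are all-cause failures, not cholangiopathy. The hypotheses are not labelled as 90-day rates, although they follow a list of rates most of which are so labelled. Given the stated onset, losses by day 90 would mostly not be cholangiopathy. The relevant group is grafts lost to it before month 10, for which no rate is given.
- **A bias towards no difference.** Early loss in high-risk grafts could act that way, but suspicion-driven imaging could act in the opposite direction.

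**Conclusion.** The concern holds as a conflict within the protocol article. Under the stated measurement, 90-day cholangiopathy incidence cannot be determined, grafts lost to cholangiopathy before month 10 are not counted in the 365-day incidence, and the rule cannot apply to the segment that supplies about 85% of the planned patients. The donor-type comparison in objective #6 therefore depends on how cases are found, to an extent and in a direction that the document does not allow one to state.

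This rests on taking the imaging sentence at its word. If the supplements hold dated clinical diagnoses, the defect is one of definition and is easily repaired. The prediction of allograft failure, which is defined by retransplant or death, is unaffected. The point should be settled before the cholangiopathy analyses are run, but it does not threaten the primary objectives.

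**What to change.** Reconcile Table 2 (#6), Table 3, Outcome measures and Qualitative variables as follows:

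1. Define the event as the first recorded evidence of ischemic or non-anastomotic biliary disease up to day 365, dated to that evidence, from data the centers already record and by the same definition in both segments. Use the 10–12 month MR for confirmation and grading.
2. Estimate 365-day incidence as a cumulative incidence, with death and other graft loss as competing events. Events first seen on the late MR will carry the scan date, so the day-365 value can be interpreted but the shape of the curve before it should not be over-read.
3. Report the share of patients imaged by graft type, so that readers can judge how far ascertainment differs.
4. Drop the 90-day cholangiopathy comparison, or make it descriptive, unless dated early events are available.
5. State whether cholangiopathy-free survival counts death and graft loss as events.

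The cost is revised endpoint wording and a derived variable, with no added imaging and no change in care, provided the recorded fields hold dated evidence; that should be checked against the variable lists. There are two downsides: one listed 90-day outcome is lost or downgraded, and ascertainment from records is less uniform than a central MR reading.

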#### Quantitative variables

Quantitative variables will be first explored by missing analysis at three levels: at center level, at country level, and at geographic area level.

Then, quantitative variables will be assessed by descriptive analysis in the overall population and according to three main graft types. In depth, they will be described either by mean or standard deviation (SD), whether normally distributed, or by median and interquartile range (IQR), otherwise. The Shapiro–Francia test will previously assess distribution of quantitative data.

Differences between the three main graft types ‘subgroups will be investigated using either one-way ANOVA, if normally distributed, or otherwise by the Kruskal–Wallis non-parametric test. The significance level will be set at < 0.05.

Donor characteristics, preoperative data, intraoperative data, graft histology data, and postoperative outcome-data will be also assessed as potential predictors of the main outcome, i.e., allograft survival, as well as of patients’ survival at 90 and 365 days. The characteristics mentioned above will also be implemented in algorithms to choose the best time-window within which undergoing retransplant.

The impact of donor age, graft percentage of macro-steatosis, donor warm ischemia time, donor asystolic warm ischemia time, recipient warm ischemia time, cold ischemia time, incidence of post-reperfusion syndrome, length of hospital stay, incidence of vascular thrombosis, and biliary complications (anastomotic and non-anastomotic) will be evaluated about the graft type. These characteristics will also be implemented in algorithms to evaluate the best time-window for retransplantation [14, 40–50].

The list of the definitions and abbreviations is detailed in supplementary material 2.

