 Timely prediction of AF is pivotal to identifying patients who may potentially benefit from a rescue retransplant before severe complications develop. When massive cytolysis and clear signs of liver failure occur within the first 2–4 days after LT, the indication for retransplantation is clear. Diversely, the decision to retransplant a patient with a milder degree of AF (also called dysfunction) is more challenging, especially after the first 5–10 postoperative days. AF results from a complex interplay between donor, procurement-related, and recipient perioperative factors, all of which contribute to the severity of the ischemia–reperfusion injury. Conversely, the ability of an allograft to recover from such injury is similarly impacted by numerous perioperative events (e.g., preoperative cardiac ischemic damage, frailty–sarcopenia, graft rejection, drug toxicity, kidney failure, or sepsis), [23–31] many of which are poorly studied. Although L-GrAFT and EASE scores accurately predict AF with excellent discrimination, these existing models have not specifically elucidated the role of perioperative events on the need for retransplantation [1, 2, 17]. Notably, this literature is exclusively based on retrospective, single-center studies which have not considered the center-volume effect, with a limited number of DCD and ECD grafts and no evaluation of the possible mitigation effect of MP technologies [1, 2]. The IMPROVEMENT project was designed to pay particular attention to these shortcomings, to capture and analyze as many of these qualitative and semi-quantitative variables as possible to build a comprehensive model that may meaningfully predict AF and guide treatment decisions regarding retransplantation. The study objectives are detailed in Table 2.

**Table 2 Tab2:** Study objectives

Primary (#1)	To make a snapshot of the liver transplant activity on a global basis
Primary (#2)	To develop new algorithms for the timely prediction of Allograft Failure at 90 and 365 days using a comprehensive prospectively collected dataset based on the current clinical practice of liver transplant centers
Secondary (#3)	To validate the already existing predictive models and the newly developed algorithms on a retrospective cohort of patients from intermediate to high medium-volume transplant centers;
Secondary (#4)	To develop a novel time-based dynamic algorithm, with increasing accuracy from the 3^rd^ to 7^th^ post-operative day;

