### Statistical analysis plan

First, a cumulative incidence of allograft failure will be calculated. To define the best time for retransplant, different strategies may be implemented, based on the collected data at study end. As first choice, we will first draw a Kaplan–Meier for each risk stratum (i.e., each graft subtype). Then, we will analyze all potential risk factors for AF in each subtype by univariate and multivariate Cox regression models. Finally, we will implement these results in a temporal algorithm based on Cox curves to identify potential time windows for retransplant. In the case of multiple drops in the initial KM curves of similar duration, we will build the algorithm so to uniform the duration of each time-window. Alternatively, we can implement a change-point analysis model derived from Kaplan–Meier estimation of the survival function followed by the least-squares estimation of the change point [51], or a wavelet analysis of change-points based on a non-parametric hazard model [52]. We could also determine the different time windows by using an extension of Glazer’s method, using a mixture of two gamma distributions, hypothesizing two or more turning points [53]. Another possibility is represented using a Bayesian approach to the problem of hazard change with unknown multiple change-points by implementing a stochastic approximation Monte Carlo algorithm for efficient calculation of the posterior distributions [54]. Particularly used in graft failure prediction. Also, a joint latent change-point class model could represent a potential way to improve the prediction of fixed time windows for retransplantation [55, 56]. All these potential applications would depend on the data distribution at the end of data collection and events observed during the follow-up period.

Notably, since the percentage of adoption of machine perfusion is expected to be one of the main differences between the two study segments, although heterogeneously worldwide, models will be adjusted according to this parameter.i.Subgroups and interactions.

The incidence of AF at 90 and 365 as well as the incidence of death at 90 and 365 days will be calculated. Differences between the three main graft types subgroups will be investigated using either one-way ANOVA, if normally distributed, or otherwise by the Kruskal–Wallis non-parametric test. The Chi-square test will instead assess differences between qualitative variables. The significance level will be set at < 0.05.

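### Post-operative outcome data are admitted as predictors with no limit on when they become known, although final length of stay and late complications are unknown at the intended prediction time

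*Protocol article*

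**What the plan says.** All references are to the protocol article.

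- **Predictors.** The section on quantitative variables says that "postoperative outcome-data will be also assessed as potential predictors of the main outcome", namely allograft survival, and also patient survival, at 90 and 365 days. No limit is set on when these data are measured. The same paragraph sends them to the algorithms for choosing the retransplant window.
- **Named variables.** The next paragraph lists several variables, of which "length of hospital stay, incidence of vascular thrombosis, and biliary complications (anastomotic and non-anastomotic) will be evaluated about the graft type". It then adds: "These characteristics will also be implemented in algorithms to evaluate the best time-window for retransplantation".
- **Model.** The section headed Statistical analysis plan gives the first-choice route to those algorithms: Kaplan–Meier curves by graft subtype, then "we will analyze all potential risk factors for AF in each subtype by univariate and multivariate Cox regression models", then a temporal algorithm built on the Cox curves. No prediction time, landmark or time-dependent covariate is mentioned.
- **Outcome.** AF is "graft failure (leading to retransplant or death) for any reason at day 90 and at day 365 after LT". The same section continues: "Other outcome measures are comprehensive complication index, intensive care unit length of stay, hospital length of stay (LoS".
- **Complications as outcomes.** Secondary objective 8 (Table 2) is "To investigate the association of kinetic algorithms with development of post- LT complications", and ischemic cholangiopathy is among those complications.
- **Prediction time.** Secondary objective 4 (Table 2) is "To develop a novel time-based dynamic algorithm, with increasing accuracy from the 3^rd^ to 7^th^ post-operative day".
- **Cholangiopathy.** Under Qualitative variables, it is measured by cholangio-MR at 10 to 12 months, on clinical suspicion.
- **Early failures.** Under missing data management, patients retransplanted or dead before day 10 are left out of algorithm development.

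**The concern.** A prediction model may use only what is known when the prediction is made. Two kinds of admitted variable can break this rule.

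1. **Final length of stay.** Death ends the stay, so an early death forces a short one. The covariate is then partly a record of the outcome. This is truncation by the outcome rather than classical immortal time.
2. **Events that need time to occur.** A patient has to keep the graft long enough to have a later biliary complication, or a cholangiopathy read at 10 to 12 months. If such an event is coded as ever/never from transplant, the event-free time before it is credited to the complication group.

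If either happens, coefficients are distorted and apparent discrimination is raised by values that do not exist at the bedside on days 3 to 7. The Introduction and Discussion say that the models are meant to support retransplant decisions, so the point has practical weight.

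**Working it through.** No figure in the article depends on covariate timing, so there is none to reproduce. The check asks how far a covariate with **no true effect** would be distorted, with and without the day-10 exclusion.

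**Inputs**
- From the article: AF of 6% (section on study size; taken here at 90 days); exclusion of failures before day 10.
- Assumed: constant hazard; planned stay log-normal, median 14 days, log-SD 0.6; complication in 15% of patients, exponential onset with median 30 or 180 days, recorded if it occurs before failure and by day 365.

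Hazard: λ = −ln(0.94)/90 = 0.0006875 per day. T is the time to failure and S the planned stay. Observed stay is min(S, T).

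**Length of stay, no exclusion**
- P(T<7) = 1 − exp(−7λ) = 0.0048. P(S<7) = Φ((ln 7 − ln 14)/0.6) = Φ(−1.155) = 0.124.
- P(observed stay <7) = 1 − 0.876 × 0.9952 = 0.1282.
- AF by day 90 in that group = (0.0048 + 0.124 × (0.06 − 0.0048))/0.1282 = 0.01165/0.1282 = 9.1%.
- Stay over 28 days requires T>28, so AF = 1 − exp(−62λ) = 4.17%.
- Ratio 9.1/4.17 = 2.2, with no true effect.

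**Length of stay, failures before day 10 excluded**
- A stay under 7 days is now always a true discharge, so AF = 1 − exp(−80λ) = 5.35%.
- Stay over 28 days is unchanged at 4.17%. Ratio 5.35/4.17 = 1.28.

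**Complication coded ever/never, failures before day 10 excluded**

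Let μ = ln 2/median onset. Per patient destined to have the complication:
- a = ∫ from 10 to 90 of λe^(−λt)(1 − e^(−μt)) dt, the chance of failing in that interval after the complication;
- b = the chance of surviving day 90 and having the complication before failure and by day 365.

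AF with the complication = a/(a + b). All failures between days 10 and 90: exp(−10λ) − 0.94 = 0.0531. AF without = (0.0531 − 0.15a)/(0.0531 − 0.15a + 0.94 − 0.15b).

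| Median onset | a | b | AF with | AF without |
|---|---|---|---|---|
| 30 days | 0.0338 | 0.9364 | 3.5% | 5.7% |
| 180 days | 0.0091 | 0.6774 | 1.3% | 5.8% |

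Without the exclusion, the 30-day case gives 3.5% against 6.4% (a = 0.0345, total failures 0.06), so the exclusion changes little. If only complications up to day 90 are counted, b falls to 0.8225 and 0.2753, and the contrasts are 3.9% against 5.6% and 3.2% against 5.4%.

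**Cox models** (simulation, n = 4,000, 40 replicates, true hazard ratio 1.00, 15% frequency, no day-10 exclusion)

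| Horizon | Median onset | Ever/never | Time-dependent |
|---|---|---|---|
| 90 days, AF 6% | 10 days | 0.85 | 1.03 |
| | 30 days | 0.59 | 0.97 |
| | 180 days | 0.52 | 0.96 |
| 365 days, AF 10% (assumed) | 10 days | 0.91 | 0.96 |
| | 30 days | 0.89 | 1.03 |
| | 180 days | 0.55 | 0.98 |

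Time-dependent coding of the same data removes the distortion. Early-onset events are affected least.

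**The case against.** **A stronger reading is tempting.** A reader might infer that the protocol names length of stay, thrombosis and biliary complications as predictors of graft survival and so builds immortal-time bias into its models. The text does not go that far.

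- The sentence on predictors of survival names none of the three. They come in the next paragraph, first for comparison across graft types, which is legitimate, and then for the retransplant algorithms. They reach AF models only through the Cox step in the analysis plan.
- Fixed coding from the day of transplant is nowhere stated. Cox models accept time-dependent covariates, the Cox route is only a first choice, and a joint latent change-point class model is among the alternatives. Coding detail may lie in a fuller plan that is not shown.
- The day-10 exclusion removes most of the length-of-stay contrast.
- Thrombosis can be early and a real cause of failure; the article itself counts vascular and biliary events as determinants of AF. A harmful effect could outweigh the bias, so the fitted coefficient need not look protective.

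All of this stands and narrows the point. It does not remove it. The article states a rule on inputs, and that rule admits outcome data without a time limit. The day-10 exclusion fixes who is analysed, not which covariate values may be used, and the complication contrast survives it. Careful coding can rescue dated complications, but not a final length of stay that failure itself cuts short.

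**Conclusion.** The point holds in a limited form. The protocol admits post-operative outcome data as predictors, and puts length of stay and complications into algorithms built on AF models, without tying any of them to a time of prediction. Final length of stay is also a study outcome. Cholangiopathy, taken here to fall within non-anastomotic biliary complications, is read at 10 to 12 months. Neither is known on days 3 to 7.

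Immortal-time bias is conditional on ever/never coding from transplant. Under that coding, and after the day-10 exclusion, a null complication shows AF at 90 days of 3.5% against 5.7% (30-day median onset) or 1.3% against 5.8% (180-day). For length of stay about 5.35% against 4.17% remains. Onset, frequency, stay distribution and hazard shape are assumptions that the article does not supply, so the direction of the bias is firmer than its size.

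The criticism does not extend to AST, platelets, bilirubin and INR known by the prediction day, which are proper predictors.

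**What to change.** State a prediction time (landmark day) for every AF, survival and retransplant-window model, and admit only variables known by that day. Early AST, platelets, bilirubin and INR stay in. Enter thrombosis and biliary events either as time-dependent covariates or as having occurred by day k. Keep final length of stay as an outcome only and take it off every list of model inputs; its comparison across graft types can remain.

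The change is to analysis wording. It has two costs: event dates must be available for the complications, and patients who fail before a landmark leave that model, so their number should be reported for each landmark.
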